### Study procedures

**
*Inclusion criteria*
**

•   A history of fever at presentation for ≥ 72 hours and a documented fever (≥37.5°C (axillary) or ≥38°C (oral))

•   Age ≥ 2 years (and ≥ 10kg) to 65 years

•   No clear focus of infection on initial clinical evaluation

•   Malaria rapid diagnostic test (RDT) negative; dengue non-structural protein NS1 RDT negative; scrub typhus RDT negative; C-reactive protein (CRP) rapid test ≥10 mg/L

•   Able to take oral treatment

•   Able to attend for follow-up and can be contacted by telephone

•   Written fully informed consent to participate in the study including assent for children in addition to parental/legal guardian consent.

**
*Exclusion criteria*
**

The participant may not enter the trial if ANY of the following apply:

•   History of fever for >14 days

•   Pregnant or positive pregnancy test or breast-feeding

•   Presence of clinical symptoms or signs indicating a focal infection such as pneumonia; urinary infection, meningitis, eschar

•   Obtundation, haemodynamic shock, visible jaundice, gastrointestinal bleeding or any signs of severe disease that may require immediate hospitalisation

•   Being treated for tuberculosis (TB) or human immunodeficiency virus (HIV) or severe acute malnutrition

•   Patients with cardiac disease

•   Patient requiring intravenous antibiotics for any reason

•   Previous history of hypersensitivity to any of the treatment options

•   Either of the trial drugs are contraindicated for any reason (e.g. drug interactions)

•   Has received azithromycin or cefixime in the last five days

•   Receiving another antimicrobial and responding clinically to the treatment as judged by the attending clinician.

•   Being on another drug (for example certain kinds of anti-depressants, or anti-convulsants) that may also cause prolonged QT interval

•   Positive polymerase chain reaction (PCR) test for coronavirus disease 2019 (COVID-19) before or after randomisation

**
*Screening and eligibility.*
** The non-specific clinical presentation of typhoid fever can make it difficult to distinguish typhoid from other causes of an acute undifferentiated febrile illness such as malaria and dengue based on clinical history, physical examination and initial laboratory investigations alone
^
28,
30
^. There are no satisfactory rapid diagnostic tests for typhoid fever
^
31
^, and patients are treated for presumed typhoid fever (in high typhoid fever incidence areas) or fever without a focus that require antimicrobials (in low enteric fever incidence areas). We will use the RDTs available for other common causes of fever in our region to rule out malaria, dengue, and scrub typhus, and a CRP cut-off to select the sub-group of patients more likely to have a bacterial infection such as typhoid fever. In a large fever study from South East Asia, a CRP at a threshold of 10mg/L had sensitivity for detecting bacterial infections of 95% with a specificity of 49%
^
32
^. In 251 adults and children with blood culture positive typhoid fever in Vietnam, 242 (96.4%) had a CRP ≥10mg/L at presentation ([name], unpublished data). In addition, with the appearance of COVID-19, this disease will have to be kept in the differential diagnosis as a cause of suspected or confirmed typhoid fever. We plan to do a PCR test for COVID-19 after randomization of our patients as there is usually a 24 hour test turnaround time. If the patient tests positive, the patient will be taken out of the study and followed up in a regular fashion as per the local hospital rules. The screening for COVID-19 will be site specific and may be based on reverse transcription polymerase chain reaction (RT-PCR) or antigen testing as per the local guidelines of the country.

**
*Informed consent.*
** Prospective, written informed consent will be obtained from the participant, or the parent or person with legal responsibility (including legal authorities) for a child (if participant’s age is ≤ 18 years old), after explanation of the aims, methods, benefits and potential hazards of the trial and before trial specific procedures are performed. The consent forms can be found as extended data
^
29
^. Any patients potentially eligible for the study will be screened by the research nurse (RN) and community medical auxiliaries (CMA). Those meeting the criteria will be approached for informed consent by the study doctor.

Written and verbal versions of the participant information and informed consent will be presented to the participant, or the parent or person with legal responsibility for a child, detailing: the exact nature of the trial; what it will involve for the participant; the implications and constraints of the protocol; the known side effects and any risks involved in taking part. It will be clearly stated that the participant, or the parent or person with legal responsibility for a child, is free to withdraw from the trial at any time for any reason without prejudice to future care, without affecting their legal rights and with no obligation to give the reason for withdrawal. The participant, or the parent or person with legal responsibility for a child, will also be informed that they can choose to have their remaining blood samples destroyed and not stored for future analysis at the end of the trial.

The participant, or the parent or person with legal responsibility for a child, will be allowed time to consider the information, and the opportunity to question the Investigator or other independent parties to decide whether they will participate in the trial.

The participant, or parent or person with legal responsibility a child, must personally sign and date the latest approved version of the informed consent form. For children, where understanding is considered adequate, they will be asked to sign the assent form as per local ethics committee guidance. For children below the considered age, assent will be verbal, along with the consent from guardian. The person who obtained the consent must be suitably qualified and experienced, and have been authorised to do so by the Chief/Principal Investigator. A copy of the signed informed consent will be given to the participant. The original signed form will be retained at the trial site.

If the participant, or the parent or person with legal responsibility for a child, is illiterate then a third party independent of the study may act as a witness to attest that the information in the consent form and any other written information was accurately explained to, and apparently understood by, the participant, or the parent, or person with legal responsibility for a child, and that informed consent was freely given. In this event, the witness will also sign and date the consent form.

**
*Randomisation and treatment allocation.*
** Participants will be randomly allocated to one of two treatment arms resulting in a 1:1 final disposition. The statistician in charge of randomization list preparation will set up statistical code to generate the randomization list and transfer it to the study pharmacist in accordance to the standard operation procedures (SOPs). The study pharmacist will then change the random seed, i.e. the initialization of the random numbers generator, in the statistical code in order to blind the biostatistician and then run the code to prepare the final randomization list. The generated randomization lists will be securely incorporated within the trial database. A reliable manual back-up system will also be available. The computer-generated randomisation list will use block randomization with stratification by site and age (children <16 years) and adults (≥16 years). The recruitment in most sites will take place during working hours as these are uncomplicated typhoid patients.

Randomisation will be performed using a web-based system accessed using an authorized username and password at each site and administered by the Oxford University Clinical Research Unit- Nepal Clinical Trial Unit independent from the study. Before treatment allocation the patient’s eligibility and informed signed consent will be confirmed and entered into the database. The allocation code will be held by the CTU pharmacist in Nepal.

### Study intervention

**
*Initial trial visit.*
** Once consented, the following procedures will be completed and all details will be recorded in the case report form (CRF).

1. A member of the study team will collect demographic information (including age and address) and participant contact details.

2. A history and full physical examination will be performed. This will include current and past medical history and medications. Height/length and weight will be collected for all children <5 years of age.

3. Any additional laboratory samples will be collected and all available results will be reviewed (
Table 2: Schedule of events)

4. Upon successful randomisation, the clinician should then prescribe the trial drugs. Both the clinician and the patient will be blinded.

5. A study card containing the name of the study, and contact details for the study team will be given to the participant or the participant’s parents or person with legal responsibility to call if they have any concerns, or if admitted to hospital at any time during the duration of the study. The card will also contain instructions to attend the study clinic, if the participant becomes more unwell during the study period. Participants or participant’s parents or person with legal responsibility will be given details of the follow-up appointments.

**Table 2. T2:** Schedule of events.

		Days following enrolment									
Study day	0	1	2	3	4	5	6	7	14	28	90 ^ 1 ^
Eligibility assessment	X										
Haematology(1mL)	X							(X) ^ 2 ^			
Biochemistry(1ml)	X							(X) ^ 2 ^			
Blood Culture (3/8ml)	X							X			
Blood for RDTs	X										
Blood for storage (1mL)	X									X	
Informed consent & patient information	X										
Urine stored antibiotic activity bioassay	X										
Stool culture/storage	X ^ 3 ^							X ^ 3 ^	X ^ 3 ^	X ^ 3 ^	(X) ^ 3 ^
Nasopharyngeal swab PCR/Antigen for COVID 19	X										
Randomization	X										
Drug Administration	X	X-X	X-X	X-X	X-X	X-X	X-X	X ^ 4 ^			
Hospital visits	X							X	X	X	(X)
CMA home visits			X		X						
Telephone calls	X	X-X	X	X-X	X	X-X	X-X				
Temperature *	X	X-X	X-X	X-X	X-X	X-X	X-X	X ^ 4 ^			
Adverse event assessment	X	X	X	X	X	X	X	X	X	X	

[
^1^Followup on day 90 if the day 0 blood culture or faecal culture positive for
*S*. Typhi or
*S*. Paratyphi;
^2^Haematology and biochemistry repeated if day 0 results abnormal;
^3^Stool cultures for
*S*. Typhi or
*S*. Paratyphi on day 0, 7, 14, 28. Also on day 90 if the day 0 blood/stool culture positive for salmonella.
^4^If still febrile on day 7 twice daily assessments will continue until afebrile for48hrs and further treatment may be required as determined by the Trial Physician] PCR=polymerase chain reaction, COVID-19=coronavirus disease 2019, RDT=rapid diagnostic test. *37.5 degrees C axillary temperature.

**
*Follow-up trial visits.*
** There will be routine participant follow-up via telephone or face-to face contact twice a day for the first seven days of antimicrobial treatment (and longer if the symptoms have not resolved). Caregivers are instructed to be consistent and measure temperature always at the same location (oral or axillary, not either or) for each patient and approximately at the same time. Face to face follow up by participant attendance at the clinic will be at 7 days, two weeks and one month. For patients who had positive blood or stool culture for
*S.* Typhi or
*S*. Paratyphi at the time of presentation there will be a final clinic follow-up at three months.

The telephone calls will be made to ensure that clinical progress is satisfactory and for monitoring of symptoms. Any problems faced by participants can be discussed and possible adverse effects identified.

Community medical assistants (CMA) will visit the patients at their home on day 2 and day 4 of treatment to ensure that clinical progress is satisfactory and for monitoring. Special attention will be paid to the assessment of adherence to study medications, drug-related adverse events and disease related events. Adherence will be assessed using standardised questionnaires and pill counts. At the first visit their home location will be recorded using global positioning system (GPS).

All patients will return to the clinic for follow-up on day 7, day 14, day 28 (and day 90 if typhoid fever confirmed at onset) after the start of treatment for follow up clinical history, physical examination and sampling.

To ensure an optimal retention rate, the participants will be contacted by phone to remind them of their next visit. In addition, patients who have missed a visit will be contacted by phone for a maximum of three times after which a maximum of three home visits can be conducted. All contact attempts will be recorded.

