## Introduction

Typhoid (caused by
*Salmonella enterica* serovar Typhi) and paratyphoid fever (caused by
*Salmonella enterica* serovar Paratyphi A), collectively referred to as typhoid fever in this protocol, are common causes of non-specific febrile infection in adults and children presenting to health care facilities in low resource settings such as the South Asia region
^
1–
4
^. South Asia has been described as the largest hub for typhoid fever in the world and antimicrobial resistance has become a critical issue
^
5
^. In the last 20 years, treatment of typhoid fever with a 7-day course of a single oral antimicrobial, such as ciprofloxacin, cefixime or azithromycin, given in an out-patient setting has led to patient recovery in 4 to 6 days without the need for expensive hospitalization. Increasing antimicrobial resistance in Asia and sub-Saharan Africa threatens the effectiveness of these treatments and increases the risk of prolonged illness and severe disease.

The fluoroquinolone class of antimicrobials have been a common choice to treat typhoid fever across South Asia during the last two decades. Now low and high-level resistance is so widespread that the entire class is no longer a reliable treatment choice
^
2,
6
^. Cefixime and azithromycin are commonly recommended alternatives and widely used
^
7–
11
^, but the conflicting results from small randomised controlled trials (RCTs) with cefixime and azithromycin in typhoid fever leave many clinicians unsure about the optimum antimicrobial treatment for typhoid fever in this region.

The outcome for patients treated with cefixime (10–20mg/kg/day for 7–14 days) in typhoid fever are particularly mixed with prolonged fever clearance times of 6–8 days, clinical failure rates of between 6% and 27% and microbiological failure rate between 0% and 4.5%
^
12–
15
^. The reported fever clearance times with azithromycin treatment (10–20 mg/kg/day for 5–7 days) is usually 4–6 days and clinical failure rates range from 0% to 18% with a microbiological failure rate from 0% to 3.2%
^
7,
16–
23
^. A number of the studies with azithromycin have demonstrated a delayed microbiological clearance, indicated by positive blood culture during the treatment course
^
17,
19–
21,
23
^. Azithromycin activity is predominantly intracellular with studies from Vietnam indicating that up to one third of
*S.* Typhi may be found in the extracellular compartment
^
24,
25

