### Objectives

**
*Primary objective*
**

To determine whether combined treatment with seven days of an azithromycin and cefixime is superior to seven days of azithromycin and placebo in preventing treatment failure in patients with clinically suspected or confirmed uncomplicated typhoid fever.

**
*Secondary objectives*
**

To compare the fever clearance time (FCT) in patients in each treatment armTo compare the time from onset of treatment to treatment failure in patients in each treatment armTo compare the time from onset of symptoms to treatment failure in patients in each treatment armTo compare the occurrence of adverse events in each treatment armTo compare the clearance of faecal carriage of
*S*. Typhi or
*S.* Paratyphi in the patients with blood culture confirmed typhoid fever at onset in each treatment armTo compare the cost-effectiveness of the treatment in each treatment arm

**
*Exploratory objectives*
**

To determine the pharmacokinetics of each drug in the two treatment armsTo determine the diagnosis in participants who do not have blood culture confirmed typhoid feverTo compare the faecal micro biome of patients with confirmed and suspected typhoid fever

**
*Endpoints*
**

*Primary endpoint*

A composite outcome of treatment failure by the 28th day after the initiation of treatment will be defined by either of the following events: 1.Clinical failure: persistence of fever on day 7 (168 h) post treatment initiation OR The need for rescue treatment as judged by the Trial Clinician OR The development of any complication (e.g., clinically significant bleeding, fall in the Glasgow Coma Scale score, perforation of the gastrointestinal tract) OR Syndromic enteric fever relapse within 28 days of initiation of treatment. 2.Microbiological failure: a positive blood-culture for
*S.* Typhi or
*S*. Paratyphi on day 7 of treatment regardless of the presence of fever (microbiological failure) OR blood culture-confirmed typhoid fever relapse within 28 days of initiation of treatment.

*Secondary endpoints*

1. The fever clearance time (FCT) will be the time from the first dose of a study drug until a temperature of < 37.5°C (axillary); < 38.0°C (oral) has been achieved for at least 48 hours

2. The time to treatment failure will be the time from the first dose of a study drug until an event occurs defined as a treatment failure

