3. The time to treatment failure will be the time from the day of the first symptom until an event occurs defined as a treatment failure. As subjects are only under observation from the initiation of treatment onwards, they will be considered as left-truncated at that timepoint.

4. Adverse events will be graded (grade 3/4 adverse events, serious adverse events, adverse events of any grade leading to modification of study drug dose or interruption/early discontinuation)

5. Positive culture of faeces sample for
*S*. Typhi or
*S*. Paratyphi with timepoints explicitly stated.

6. The incremental cost-effectiveness ratio (ICER) will comprise of the total costs per case, real outpatient and in-patient costs, total direct and indirect costs for the family and healthcare system and health outcomes converted to disability adjusted life years (DALYs). The cost per DALY averted will be compared against multipliers of the gross domestic product (GDP)/capita in each of the four countries to establish the cost-effectiveness of the combination regimen.

7. Additional diagnostic tests on the samples collected from participants who do not have blood culture confirmed typhoid fever

8. Analysis of the faecal microbiome in collected faecal samples

*Assessment of endpoints*

Participants, or their family members, will be trained how to monitor the temperature and then contacted on a twice daily basis by telephone for monitoring and recording of temperature and enquiry using symptom checklist. Temperature and symptom logs will be maintained during the twice daily telephone calls to measure fever clearance time and when the patient is seen on day 7. Each enrolled subject will measure temperature either in the axillary area or orally and stick to one method and not interchange so the documentation will not be confusing. If there is persistence of fever and/or symptoms on day 7 the patient will be reassessed, rescue treatment administered if appropriate and the patient will be judged to be a treatment failure. In addition, adverse events or signs of any complication (using a check list) developing at any time will be closely monitored and patients will be referred to the hospital if necessary, under the supervision of one of the trial physicians.

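### Neither trigger for recording temperature after day 7 matches the 48-hour definition of fever clearance, so clearance after about 120 h goes unconfirmed in participants who are afebrile and well on day 7

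*Protocol article*

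**What the plan says.** All references are to the protocol article.

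- **Objectives, Secondary endpoints, item 1.** Fever clearance time (FCT) runs from the first dose "until a temperature of < 37.5°C (axillary); < 38.0°C (oral) has been achieved for at least 48 hours".
- **Objectives, Primary endpoint.** Day 7 is fixed in hours: "persistence of fever on day 7 (168 h) post treatment initiation".
- **Objectives, Assessment of endpoints.** The FCT readings come from the "twice daily telephone calls to measure fever clearance time and when the patient is seen on day 7".
- **Table 2, Schedule of events.** Temperature is listed on day 0, twice daily on days 1 to 6, and once on day 7. None is listed for days 14, 28 or 90. Telephone calls end on day 6.
- **Table 2, footnote 4.** The only extension in the schedule is: "If still febrile on day 7 twice daily assessments will continue until afebrile for48hrs".
- **Follow-up trial visits.** Contact by telephone or in person is "twice a day for the first seven days of antimicrobial treatment (and longer if the symptoms have not resolved").
- **Introduction.** FCT under azithromycin is put at 4 to 6 days. Cefixime alone, which is not a trial arm, is given "prolonged fever clearance times of 6–8 days".
- **Statistical and analytical plans.** FCT is treated as interval-censored, estimated by the NPMLE and compared with a Weibull accelerated failure time model.

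**The concern.** The endpoint and the schedule use different conditions. The endpoint needs 48 afebrile hours. Recording continues after day 7 only if the participant is febrile that day (footnote 4) or still has symptoms (follow-up text). Someone who became afebrile at 130 h or 155 h and has recovered by day 7 meets neither condition. Recording ends before the event in the definition can be observed. A participant still febrile on day 7 is followed to the full 48 hours.

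FCT is the first secondary endpoint. It is analysed in both the ITT and the culture-confirmed populations and has planned subgroup analyses. Readings that were never taken cannot be recovered by analysis. Interval censoring deals with gaps between readings, not with a missing confirmation period. The analyst must either treat these participants as not yet cleared or count a clearance that the definition does not accept. Who is observed further also depends on day-7 status, which treatment can affect.

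**Working it through.** **1. The plan's own computed figure.** The sample-size section states 92% power for 15% against 9%, with 750 per arm and up to 10% loss. With 750 × 0.9 = 675 per arm:

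SE = √[(0.15×0.85 + 0.09×0.91)/675] = 0.0176; 0.06/0.0176 − 1.96 ≈ 1.45; power ≈ 92.6% (92.5% with the pooled variance under the null).

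The figure reproduces. It concerns the primary endpoint, whose day-7 fever component needs no 48-hour run, so nothing below touches it.

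**2. Latest clearance that can be confirmed by day 7.** I take clearance as the start of the 48-hour run.

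168 h − 48 h = 120 h.

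With readings 12 h apart, first afebrile readings at 132, 144, 156 and 168 h all leave less than 48 h on record. The 120–168 h window covers the upper half of the stated azithromycin range (120–144 h of 96–144 h) and the 24 h beyond it.

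**3. Share of participants in the window.** The article gives no FCT distribution. I assume a Weibull, the family the plan names for its model, with median m and shape k:

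S(t) = exp[−ln 2 · (t/m)^k]; share = S(120) − S(168).

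Example, m = 120 h, k = 2: S(120) = 0.500; S(168) = exp(−0.693 × 1.4²) = 0.257; share = 0.243.

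| Median | k = 1.5 | k = 2 | k = 3 |
|---|---|---|---|
| 72 h (3 days) | 14.1% | 12.3% | 4.0% |
| 96 h (4 days) | 17.9% | 21.9% | 23.4% |
| 120 h (5 days) | 18.3% | 24.3% | 35.1% |
| 144 h (6 days) | 17.3% | 22.9% | 33.7% |

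Medians of 4 to 6 days give 17–35%. The 3-day row reflects the only combination figure in the article, from travellers with paratyphoid fever given azithromycin plus ceftriaxone, so it is only indicative. Averaging that row with a 4- to 6-day control arm at the same shape gives a lowest value of (4.0 + 23.4)/2 = 13.7% and a highest of (4.0 + 35.1)/2 = 19.6%, that is 14–20% overall. Participants still symptomatic on day 7 must be taken off all these shares. The article gives no figure for them.

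**4. Effect on the estimated median.** I simulated Weibull times (k = 2), grouped them into 12-hour intervals, right-censored clearances in the window at the last febrile reading, left later clearances observed, and refitted an interval-censored Weibull.

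| True median | Fitted median | Change |
|---|---|---|
| 96 h | about 103 h | 103/96 = +7% |
| 120 h | about 133 h | 133/120 = +11% |
| 144 h | about 161 h | 161/144 = +12% |

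**5. Effect on the between-arm time ratio** (same handling, k = 2, common shape). A true ratio of 0.80 (96 against 120 h) becomes 0.78; 0.83 (120 against 144 h) becomes 0.84; 0.60 (72 against 120 h) becomes 0.55. The shifts are about 2%, 1% and 8%, and not all in one direction. Repeating the last case with k = 3 gives about 0.53, so arms far apart with a narrow distribution are the least favourable case. With equal arms the ratio stays at 1.

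**The case against.** Several stronger readings are tempting, and the article does not support them.

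- **That recording stops for everyone afebrile on day 7.** The follow-up text continues twice-daily contact while symptoms are unresolved. Some people who cleared only a day or two earlier will still have symptoms, and their 48 hours may be completed. This stands and narrows the group to those both afebrile and symptom-free. It also means the article holds two triggers that differ from each other as well as from the definition.
- **That the window is the centre of the expected range.** It is the upper half of the 4 to 6 days and the day after.
- **That 17–35% of all participants are affected.** That applies a median from azithromycin alone to both arms, whereas the trial expects the combination to do better. The 14–20% figure is the fairer one if the combination median is 3 days.
- **That fever returning on days 8 and 9 would be missed.** All participants are seen on days 14 and 28, are told to attend if they become more unwell, and count as treatment failures if they relapse by day 28. A sustained recurrence would mostly be found, though its timing might be lost.
- **That the slowest responders have clean data.** Those febrile on day 7 are judged treatment failures and may receive rescue treatment, so their later clearance may not reflect study drug alone.
- **That the gap creates a false difference between arms.** With equal clearance distributions and the same handling in both arms, it does not.

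It can also be said that this is a condensed article with the analysis details left to an SAP. That is fair for how an unconfirmed clearance is coded. It does not answer the point about collection, because the article itself fixes both the definition and the conditions for continued recording.

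**Conclusion.** The point holds in limited form. The definition requires 48 afebrile hours, and neither the fever trigger nor the symptom trigger ensures they are recorded. Participants who first become afebrile between about 120 h and 168 h and are well on day 7 cannot meet the endpoint as defined.

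The 120 h limit follows from the article's own figures. The size does not: 17–35% for medians of 4 to 6 days, 4–14% for 3 days and 14–20% for the mixed case all rest on an assumed Weibull with shape 1.5–3, before removing symptomatic participants. The 7–12% lengthening of the median assumes shape 2 and right-censoring at the last febrile reading, which the article does not say it will use. Distortion of the treatment contrast is usually smaller. This is a gap in measuring one secondary endpoint that should be closed. It does not threaten the primary result.

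**What to change.** Reconcile footnote 4 and the follow-up text with the FCT definition through one measurement rule: twice-daily temperature recording continues after day 7 for every participant who has not yet completed 48 consecutive afebrile hours, whether or not febrile or symptomatic on day 7. A clearance just before 168 h would then be confirmed by about 168 + 48 = 216 h (day 9). The rule concerns recording only and changes no treatment.

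The cost is up to two more days of the existing telephone temperature calls for a minority of participants, with no new procedure. The article's study-status section reports nine patients recruited, so at that stage nearly all participants would have been covered.
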